### Data collection

Data will be collected from the online Vfrac tool. When healthcare professionals enter data into the tool after clicking on the URL, inbuilt analytics will be used to record the Vfrac score, length of time taken and completeness of data collection. For each individual patient, once the data have been submitted, the Vfrac result (low or high risk of VFF) and recommendations will be available as a ‘copy and paste’, along with a unique Vfrac code (watermark). This will then be recorded in the individual patient’s medical records. Each practice will have their own URL allowing secure access to the online Vfrac tool, and also to allow analysis of differences in data collection across practices. No patient identifiable data will be recorded by the online Vfrac tool, the data stored will include the answers to each question for every entry per practice, the resulting Vfrac score, date submitted and unique Vfrac reference code generated per record. There will be no ability to link back any data to individual patients, only to practices. The Vfrac result and recommendation for each individual patient will have been copied and pasted into the medical records at the time of the consultation and will be captured during the electronic download from the general practices every three months using the watermark.

### Follow-up

Regular data will then be collected on consultations by older women with back pain from all six general practices every 3 months for 12 months. Data will be collected by electronic download to capture type of healthcare professional carrying out initial consultation for back pain, number and date of consultations by older women with back pain, resource use after initial consultation for back pain and new diagnoses since initial consultation for back pain (Appendix 1). In addition, from intervention general practices data will be collected on proportion of consultations for back pain where Vfrac was used, other consultations where Vfrac was used, and results of the Vfrac tool recorded in the medical notes (Appendix 2). Data collected will be anonymised at each general practice to remove patient identifiable details such as name, address and NHS number.

## WP 2: nested qualitative assessment of acceptability

A total of eight focus groups will be conducted, four with patients who were assessed using the Vfrac tool and four with healthcare professionals. Focus groups will aim to understand and assess the perceived acceptability of Vfrac and identify factors that impact on implementation, including barriers and facilitators to delivery. ‘Topic guides’ for patients and healthcare professionals will be used to guide discussions, with flexibility to pursue emerging ideas [16]. These will be informed by the Theoretical Framework of Acceptability [17], a framework that has been developed to guide the assessment of acceptability for providers and recipients, and implementation science theory [18], especially theories developed to explore the implementation of complex interventions. Similarities and differences between participants’ views will be explored. Initial focus groups will inform topic guide refinement.

Patients (female aged ≥ 65) who were assessed using the Vfrac tool during a consultation for back pain in intervention practices will be identified by healthcare professionals working within the practice. They will be identified by a unique code generated and embedded within their primary care records when Vfrac was used (with the prefix ‘VFRAC’). They will be approached by the direct clinical care team in their general practice with an information pack about the study. The information pack will contain an introductory letter, a participant information booklet, a consent form and a pre-paid envelope for return to the research team. Patients will be invited to contact the study team if they have any questions. Informed consent will be by self-completion of the consent form, after they have had time to read the patient information booklet and asked any questions. Those who reply by returning the completed consent form will be recruited. The consent form will be checked, initialled and dated by a Vfrac study team member. Patients who are unwilling to provide informed consent or who do not have the capacity to provide informed consent will be excluded. Purposive sampling will be used to take into account age, comorbidities and other relevant sociodemographic characteristics [19]. An estimated 4–6 patients will be included in each focus group, totalling 16–24 patients. The final sample size will be determined by data saturation [20]. If replies to the invitation in the study information packs are low (less than the required number of 16–24), a reminder letter will be sent 4–6 weeks after the original invitation.

Focus groups with patients will be conducted either in person on University of Bristol premises or remotely using video conferencing software. If face-to-face focus groups with patients are not feasible and individuals who have been recruited do not feel they have the necessary IT skills to participate in online group discussions, to ensure maximum inclusion they will also be given the option of taking part in one-to-one interviews to be conducted face-to-face or by telephone.

Healthcare professionals from intervention practices (WP1) who used Vfrac, or were involved in the implementation of Vfrac within IT systems or clinical pathways, will be approached via their research lead. Research leads will send an invitation email to potential participants with information about the study that will ask them to contact the research team if they are interested in taking part. Participants will include a range of healthcare professionals involved in the identification of VFFs in primary care including GPs, nurses, paramedics and first contact physiotherapists. Purposive sampling will be used to account for professional roles, years of experience and other relevant characteristics [21]. Written informed consent will be sought prior to data collection. After giving consent they will be asked to provide basic sociodemographic information (age, gender, ethnicity, professional grouping) and to indicate how they have been involved in setting up or using Vfrac. An estimated 4–6 participants will be included in each focus group, totalling 16–24 healthcare professionals. As above, the final sample size will be determined by data saturation [20]. If less than the required numbers of staff have replied (16–24), a reminder email will be sent 4–6 weeks after the original.

Focus groups with healthcare professionals will be carried out remotely using video conferencing software. If focus groups with healthcare professionals are not possible given their time constraints, provisions will be put in place for individual interviews that will either be conducted face-to-face, by telephone or using videoconferencing software to ensure maximum diversity and inclusion.

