**Fig. 1 Fig1:**
[figure not shown]
The online vertebral fracture screening tool made available for use by general practitioners in three general practices across the West of England Clinical Research Network

**Table 1 Tab1:** Work packages of the Vfrac feasibility study

Work Package (WP)	Vfrac study component	Objective(s)
1	Vfrac implementation within primary care	To optimise integration of the Vfrac decision tool within primary care IT systems and clinical pathways. To determine the length of follow-up (from assessment to final management) that is required for a future trial.
2	Nested qualitative assessment of acceptability of the Vfrac tool	To understand how acceptable Vfrac is to healthcare professionals (providers) and patients (recipients) and identify factors that impact on implementation, including barriers and facilitators to delivery
3	Nested assessment of agreement between the use of Vfrac within general practices and self-completion at home	To decide whether Vfrac can be self-completed at home or whether it needs to be delivered face-to-face for any future trial.

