## WP 1: Vfrac implementation within primary care

For this work package general practices will be recruited and then assigned to either intervention or control by purposeful selection to ensure there is variation in practice size and deprivation levels in both groups. Six general practices will be recruited from the West of England region purposively, to include small and large practices and practices within different Primary Care Networks (PCNs)/clusters, which vary in deprivation as assessed by the Index of Multiple Deprivation. General practices will be approached by the West of England Clinical Research Network, which covers the Integrative Care Boards of: Bristol, North Somerset and South Gloucestershire; Bath and North East Somerset, Swindon and Wiltshire; and Gloucestershire. Using a proforma, baseline data will be collected from all six practice managers to describe their practice (Table 2).

**Table 2 Tab2:** Data collection from six general practices recruited to the Vfrac feasibility study

**Feasibility study of Vfrac implementation within primary care**	**Outputs**
Outcome measures from intervention and control practices 1.1 Descriptives of each practice -Number of registered patients -Number of women ≥ 50 and ≥ 65 -Computer system -Name of PCN/cluster -Other demographic characteristics 1.2 Type of healthcare professional carrying out initial consultation for back pain 1.3 Number and date of consultations by older women with back pain 1.4 Resource use after initial consultation for back pain including -Consultations in primary and secondary care -Referrals including rheumatology, osteoporosis clinics, geriatrics, physiotherapy, pain clinic -Investigations including DXA, radiology -New medication prescriptions 1.5 New diagnoses since initial consultation for back pain Additional outcome measures from intervention practices only: 1.6 Proportion of consultations for back pain where Vfrac was used 1.7 Other consultations where Vfrac was used 1.8 Results of the Vfrac tool completed in primary care	1. Training requirements for healthcare staff 2. IT requirements and options for ideal integration within IT systems 3. Options for ideal integration within clinical pathways 4. Required length of follow-up for any future definitive trial to capture most (> 90–95%) patient journeys 5. Contribution to understanding of ‘usual care’ for patients who consult with back pain in the control practices where Vfrac is not used

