**Nested qualitative assessment of acceptability**	**Outputs**
Outcome measures from participants recruited at intervention practices 2.1 Understanding of acceptability to healthcare professionals and patients 2.2 Identification of factors that impact on implementation, including barriers and facilitators to delivery	1. Results will form the basis of recommendations to modify Vfrac and improve delivery in any future trials

**Nested assessment of agreement between the use of Vfrac within general practices and self-completion at home**	**Outputs**
Outcome measures from participants recruited from intervention practices 3.1 Outputs of self-completion Vfrac 3.2 Satisfaction and ease of the use of self-completion questionnaire 3.3 Participants views of whether they preferred face-to-face assessment in primary care or self-completion at home 3.4 Assessment of agreement between outputs of the self-completed Vfrac and face-to-face Vfrac using Cohen’s kappa	1. Decision as to whether Vfrac can be carried out as a self-completion assessment or whether it needs to be delivered face-to-face for any future trial 2. Summary statistics for proportions of participants satisfied with process, interpersonal and technical attributes will be calculated 3. Recommendations in free-text fields of the satisfaction and ease of use questions will be used to modify the (future) tool if necessary

A clinical update on osteoporosis will be offered to all. Three practices will then be assigned to the intervention arm and three to the control by purposeful selection to ensure there are both large and small practices in both groups that have varying levels of deprivation. The control practices will use standard clinical processes for older women consulting with back pain. Those in the intervention arm will be trained in the use of Vfrac and will have it made accessible from their IT systems (through provision of a URL via pop-ups on typing relevant words such as back pain). The use of the Vfrac tool will be encouraged within their clinical pathways for management of older women (over 65 years of age) who consult with back pain. The use of the tool in a manner that is in accordance with each practice’s service delivery model will be facilitated by the research team in discussion with the clinical team. As the use of Vfrac poses only minimal/no risk, the use of a waiver of consent by individual patients for this cluster-level intervention is appropriate [15].

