One of the limitations of this feasibility study is that the use of the Vfrac tool will only be evaluated in older women and the data collected would be confined to older women. Further work is being conducted as part of a separate study to determine whether the Vfrac tool can be used to identify vertebral fractures in older men with a similar success rate to older women. We will assess the level of agreement in Vfrac outputs obtained from face-to-face completion with a research nurse and self-completion by men. Semi-structured interviews will also be undertaken to determine if the Vfrac tool is acceptable to men. Another limitation of this study is the recruitment of only six general practices which will offer only limited data that does not account for UK-wide variability in consultation, management and healthcare use for back pain. Therefore, we will collect and analyse anonymized national data acquired from the Clinical Practice Research Datalink to investigate UK-wide variability in consultation, management and healthcare utilisation for back pain in older adults. This will help understand what ‘usual care’ entails for older people with back pain and help plan future testing of the Vfrac tool.

A future parallel group cluster randomized trial will determine the clinical- and cost-effectiveness of Vfrac from the NHS perspective, compared with the standard care of older women with back pain. The stop/go criteria for a future cluster randomized controlled trial informed by this feasibility study will rely on a realistic required sample size (of up to 40 clusters), a realistic required length of follow-up (no greater than 15 months), and evidence that the Vfrac tool is acceptable to healthcare professionals and patients.

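### The WP2 staff sampling frame leaves out trained clinicians who neither used nor helped implement Vfrac, so barriers that prevented any use are likely to be missed.

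*Protocol article*

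**What the plan says.** In the protocol article, Table 1 gives WP2 two tasks: to find out how acceptable Vfrac is to providers and recipients, and to "identify factors that impact on implementation, including barriers and facilitators to delivery". The section on WP 2 defines which staff are approached: "Healthcare professionals from intervention practices (WP1) who used Vfrac, or were involved in the implementation of Vfrac within IT systems or clinical pathways". Once they have consented, participants are asked "to indicate how they have been involved in setting up or using Vfrac". Selection within that group is purposive: "Purposive sampling will be used to account for professional roles, years of experience and other relevant characteristics". Four staff focus groups of 4–6 people are planned, 16–24 in total, with the final number set by data saturation.

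The section on WP 1 describes exposure to the tool. "Those in the intervention arm will be trained in the use of Vfrac", they receive a link through pop-ups, and "The use of the Vfrac tool will be encouraged within their clinical pathways". Table 2 lists, for intervention practices only, "1.6 Proportion of consultations for back pain where Vfrac was used".

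The Discussion names three stop/go considerations for the definitive trial: a realistic sample size (up to 40 clusters), a realistic follow-up (no more than 15 months), and "evidence that the Vfrac tool is acceptable to healthcare professionals and patients".

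**The concern.** The staff best placed to say why the tool was not used are those who were given it and never took it up. The eligibility rule is written in terms of having used or implemented Vfrac, so such people come in only if they had an implementation role. Some barriers act before first use: the pop-up is ignored, the consultation is too short, the clinician doubts the value of the result, or back pain is handled by telephone. The planned participants can describe these only by reporting what colleagues have said.

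Two things are at stake. First, WP2's account of barriers goes into the manual carried forward to the definitive trial and eventual implementation, so a gap here is carried forward too. Second, staff acceptability is part of a stop/go criterion, and WP2 is the only component listed as measuring it (outcome 2.1 in Table 2).

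**Working it through.** The point concerns a sampling frame, so the check consists mainly of setting the relevant parts of the article side by side.

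1. **Planned numbers.** Four groups of 4 give 4 × 4 = 16, and four groups of 6 give 4 × 6 = 24. This reproduces the stated 16–24. No figure in the plan is in dispute.

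2. **Can trained non-users exist?** Yes. WP 1 trains intervention practices but only encourages use. Item 1.6 is an outcome only because use may be incomplete, and the Background says real-world testing is needed partly to learn whether the tool will be used at all.

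3. **Does the frame admit them?** It has two limbs: used Vfrac, or took part in implementing it. Among staff exposed to Vfrac:
   - used regularly: eligible;
   - used once or a few times, then stopped: eligible, because no minimum use is set;
   - never used, but involved in IT or pathway implementation: eligible;
   - never used and no implementation role: not eligible.

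4. **Does any other sentence let the last group in?** No. Purposive sampling by role, experience and other characteristics selects among those already eligible. The statement that participants will cover a range of professions describes the mix within the frame. The involvement question presumes some setting up or use and offers no place for non-use.

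5. **Does another component collect their reasons?** None is listed. Item 1.6 is a proportion of consultations. It shows how often the tool was used, not why it was left unused. The online tool's analytics (score, time taken, completeness) exist only for entries that were made.

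6. **Direction and size.** Suppose a fraction *u* of exposed staff is reachable under the frame, with a share *A* of them finding the tool acceptable, against a share *B* of those outside it. The favourable tilt is *A* − [*uA* + (1 − *u*)*B*] = (1 − *u*)(*A* − *B*). It is zero if the two groups think alike, and for a given positive difference it grows as *u* falls. The document gives none of *u*, *A* or *B*, and WP2 is a thematic study that estimates no proportion. The expression shows only what the tilt depends on.

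**The case against.** A reader might infer that trained non-users are excluded altogether and that acceptability will therefore be overstated. The document does not support that reading. The frame is wider than it first appears: someone who tried Vfrac once and abandoned it qualifies, as do non-users who worked on IT or pathway integration. The tool is to be fitted to each practice's service model in discussion with the clinical team, so some clinicians may qualify by that route. All of these people can report barriers, and someone may use an encouraged tool and still find it burdensome. Use is related to acceptability but is not the same thing.

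Low uptake would also not be hidden, since item 1.6 would show it, and the acceptability criterion is not expressly confined to WP2 evidence. Putting a percentage on the excluded staff would only restate an assumption about uptake. Finally, an article may leave the detailed sampling matrix and topic guides to the full protocol.

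Most of this stands, and it limits the strength of the conclusion. It does not remove the gap. The eligibility rule is stated outright in the article, so it is not a detail left to another document. People who stopped after trying, or who installed the tool, are only a partial substitute for those who never began. Item 1.6 gives a frequency without reasons, and uptake is not itself one of the named stop/go considerations, so a low figure would not automatically temper a favourable qualitative finding.

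**Conclusion.** The point holds in a limited form. Trained clinicians who never used Vfrac and had no part in implementing it cannot be invited to the staff focus groups, and no listed component asks them why. Barriers that prevented use entirely are likely to be missed or heard only indirectly, and the staff evidence for the acceptability criterion is likely to be tilted favourably. This works against WP2's own aim of identifying barriers.

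The conclusion rests on two assumptions: that some exposed clinicians will be never-users, which the optional nature of the tool makes plausible, and that their views would on average be less favourable than those of users and implementers, which is reasonable but not shown. The amount cannot be quantified from the document. If uptake among clinicians is nearly complete, the gap is small; if it is low, the gap matters for both the list of barriers and the stop/go decision. The change should be made because it is cheap and specific, but it does not invalidate WP2.

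**What to change.** - Redefine the staff frame as all professionals in the three intervention practices who were trained in or offered Vfrac, whether or not they used it, keeping those involved in implementation.
- Add level of use (none, occasional, regular) to the purposive sampling factors, with some never-users included in the same 16–24 participants.
- Extend the post-consent involvement question to include not having used the tool. Since that answer arrives only after consent, ask for level of use in the reply to the invitation as well, so that it can guide sampling.
- Say in advance that the acceptability findings will be read alongside item 1.6 when the stop/go decision is made.

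The cost is revised eligibility wording and a revised invitation email, with no increase in sample size. Ethics approval is in place and recruitment began in September 2022, so a minor amendment is probably needed. Non-users may be slower to reply; the planned reminder at 4–6 weeks and the option of an individual interview can partly offset this. If the staff focus groups have already been held, the restriction should at least be reported as a limitation of the acceptability evidence.

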### Qualitative data analysis

All focus groups and interviews will be audio-recorded, transcribed and anonymised, then imported into NVivo qualitative analysis software. They will be transcribed through an approved company (The Transcription Company UK, https://www.thetranscription.co.uk/) with a confidentiality agreement in place between the company and the University of Bristol, using a standardised protocol used for all qualitative research at the University of Bristol. After the focus group or interview has been audio recorded on an encrypted device, it will be uploaded to the University of Bristol’s secure sever as soon as possible and then deleted from the audio recorder. The data file will then be uploaded to Transcription Company’s website using an encrypted file transfer service. It will then be transcribed in full and returned. Transcripts will then be anonymised by the research team.

Data from patients and healthcare professionals will be analysed as discrete datasets, using an inductive thematic approach to identify themes and subthemes in the responses [22]. Themes from both datasets will then be synthesised. To help understand the perceived acceptability of Vfrac, an abductive approach will be used (whereby the best supporting statements for emerging themes will be linked to each theme) with codes transposed into the ‘Theoretical Framework of Acceptability’ [23]. Further factors that impact implementation will also be transposed onto the normalisation process theory [18]. To illustrate this process, data will be displayed on charts using the framework approach to data organisation [24]. Factors identified by mapping codes onto the ‘Theoretical Framework of Acceptability’ and implementation science theory will be synthesised to form a taxonomy of barriers and facilitators to implementation. These will form the basis of recommendations to modify Vfrac and improve implementation and delivery in future trials and will be recorded in a live manual (manual 1B) which will be taken forward to the future definitive trial and eventual implementation, if appropriate.

